## Supplement 1 - Trial protocol (published in *BMJ Open*)

### Introduction

Low back pain is a common presenting complaint in emergency settings. In 2015–2016 alone, there were 104 072 low back pain presentations to emergency departments in Australia, placing this condition among the top 10 reasons for emergency visits. This condition is also a common reason for emergency department presentations across the globe, accounting for 4.4% of all presentations. Unfortunately, many patients receive low-value care for their low back pain in the emergency department. Low-value care is broadly defined as the use of an intervention that provides patients with little to no benefits or causes harm. Examples of low-value care of low back pain in emergency departments include inappropriate overuse of imaging, liberal use of opioid analgesics and unnecessary admission to hospital.

Multiple clinical guidelines exist for the management of low back pain in primary care. Although it is unclear whether these guidelines should be applied in the emergency department, much of their recommendations may be relevant to emergency physicians and are often used to guide their practice. However, the mixture of providing inappropriate care and failing to provide appropriate care in the emergency department is a clear indication that healthcare is not following clinical guidelines. For instance, about 30% of patients with non-specific low back pain receive imaging in the emergency department when guidelines explicitly recommend no imaging for these cases. Imaging in the absence of suspected serious pathology does not improve patient outcomes and can potentially cause harms. Against guideline advice, around 62% of low back pain patients receive opioids in the emergency department, although efficacy in pain relief has not been established for acute low back pain and side effects are often serious, including dependence, overdose and death. Another issue is the increasing rate of hospital admissions. More than one-third of low back pain presentations to the emergency department lead to the patient being admitted to hospital, where care is likely to be similar to what could be provided in primary care.

The significant deviations from evidence-based recommendations occurring in Australian emergency departments make them an appropriate setting to trial an intervention based on improving care for low back pain. The Agency for Clinical Innovation (ACI) has recently launched a model of care for acute low back pain that could be applied in both primary care and emergency department settings. The ACI model of care was developed in collaboration with policy-makers, clinicians, consumers and researchers and distils the high-quality evidence in this area to formulate key messages for practice (table 1). Briefly, the model provides different care pathways according to a classification based on a diagnostic triage (acute or chronic non-specific low back pain, low back pain with leg pain and suspected serious spinal conditions). Risk stratification is recommended to guide the amount and type of treatment provided; including personalised evidence-based health education and treatment. Lastly, follow-up reviews are scheduled to monitor individuals' progress. Passive dissemination of guidelines, such as the ACI model of care, is unlikely to change practice. We are proposing a multifaceted strategy to implement and evaluate the ACI model of care to see if this improves health service delivery and patient outcomes for low back pain at the emergency department.

**Table 1. The key principles of the ACI model of care for acute low back pain**

|             |                                                          |
|-------------|----------------------------------------------------------|
| Principle 1 | Assessment: history and examination                      |
| Principle 2 | Risk stratification                                      |
| Principle 3 | Patient education                                        |
| Principle 4 | Active physical therapy encouraged                       |
| Principle 5 | Begin with simple analgesic medicines                    |
| Principle 6 | Judicious use of complex medicines                       |
| Principle 7 | Cognitive behavioural approach                           |
| Principle 8 | Only image those with suspected serious spinal pathology |
| Principle 9 | Predetermined times for review                           |

|              |                                                   |
|--------------|---------------------------------------------------|
| Principle 10 | Timely referral and access to specialist services |
|--------------|---------------------------------------------------|

Source: NSW Agency for Clinical Innovation. *Management of people with acute low back pain: model of care*. Chatswood: NSW Health, 2016.  
Available at: <https://www.aci.health.nsw.gov.au/resources/musculoskeletal/management-of-people-with-acute-low-back-pain/albp-model>.

## Objectives

The overall aim of the Sydney Health Partners Emergency Department (SHaPED) trial is to implement and evaluate the ACI model of care for acute low back pain. The outcomes of the trial reflect the key messages in the model: (1) patients with non-specific low back pain do not require imaging; (2) where medicines are used, simple analgesics should be the first option; (3) patients with non-specific low back pain should be managed as outpatients.

## Primary objective

The primary objective of this study is to evaluate if implementation of the ACI model of care significantly reduces the proportion of patients presenting with low back pain who receive imaging in the emergency department.

## Secondary objectives

The secondary aims of the study are:

- To determine if implementation of the ACI model of care significantly reduces the proportion of patients presenting with low back pain who receive opioids in the emergency department and the proportion of patients subsequently admitted to hospital.
- To determine if implementation of the ACI model of care significantly improves patient outcomes in people who present with low back pain in the emergency department.
- To determine the cost-effectiveness of the ACI model of care compared with current emergency department practice for people who present with low back pain.
- To determine the barriers and facilitators to the implementation intervention of the ACI model of care for people who present with low back pain in the emergency department.

## Methods and analysis

### Study design

The Standard Protocol Items: Recommendations for Interventional Trials guidelines were followed in this report of the protocol. SHaPED will use a stepped-wedge cluster randomised controlled trial design. In this study design, clusters are randomised to cross from the control period (ie, unexposed to intervention) to the intervention period at regular intervals ('steps') until all clusters have crossed to the intervention under evaluation. This design is particularly suited to interventions aiming to improve healthcare systems as all groups eventually receive the intervention. Moreover, the process allows for comparison with control sites that have not yet implemented the intervention.

In the SHaPED trial, after a retrospective baseline observation control period of 12 months prior to randomisation, the intervention will be sequentially rolled out, with a new emergency department receiving the intervention every 4 weeks, until all participating emergency departments have received the intervention. After the implementation of the ACI model of care, the emergency departments will continue using the pathways of care outlined in the model until the end of the trial (table 2).

**Table 2. SHaPED trial design**

| Steps
(clusters) | Year 1 |   |   |   |   |   |   |   |   |    |    |    | Year 2 |   |   |   |   |   |   |
|---------------------|--------|---|---|---|---|---|---|---|---|----|----|----|--------|---|---|---|---|---|---|
|                     | 1      | 2 | 3 | 4 | 5 | 6 | 7 | 8 | 9 | 10 | 11 | 12 | 1      | 2 | 3 | 4 | 5 | 6 | 7 |
| ED 1                |        |   |   |   |   |   |   |   |   |    |    |    |        |   |   |   |   |   |   |
| ED 2                |        |   |   |   |   |   |   |   |   |    |    |    |        |   |   |   |   |   |   |
| ED 3                |        |   |   |   |   |   |   |   |   |    |    |    |        |   |   |   |   |   |   |
| ED 4                |        |   |   |   |   |   |   |   |   |    |    |    |        |   |   |   |   |   |   |

Light grey: 12-month retrospective baseline control period.

Middle grey: 4-week initial intervention period.

Dark grey: sites continue with intervention plus follow-up period.

ED, emergency department; SHaPED, Sydney Health Partners Emergency Department.

## Study setting

The emergency departments of one rural and three urban hospitals in New South Wales, Australia will participate in the study: Royal Prince Alfred Hospital, Concord Repatriation General Hospital, Canterbury Hospital and Dubbo Base Hospital. Investigators in the SHaPED trial are listed in Appendix 1.

## Clinician participants

Clinician participants included in the SHaPED trial will be emergency clinical staff, such as physicians, nurses and physiotherapists, who routinely manage patients presenting to emergency departments with a primary complaint of low back pain. Potential clinician participants will be invited by the principal investigator of each emergency department and will receive a participant information statement. Research staff will verbally explain the information provided in this document to fully inform potential clinician participants of the risks and benefits of their participation. In addition, the research staff will be available to answer any questions to ensure that potential clinician participants fully understand the implications of their decision. A written participant consent form will be obtained from all participating clinicians prior to randomisation.

## Patient participants

We will use codes from the Systematised Nomenclature of Medicine—Clinical Terms—Australian version, Emergency Department Reference Set to identify low back pain presentations (Appendix 2) to the emergency departments. Presentations with codes related to low back pain with non-specific cause or those associated with neurological signs and symptoms (such as sciatica and lumbar spinal stenosis) will be included. Representations to the emergency department within 48 hours or low back pain presentations related to serious spinal pathologies (such as lumbar fracture or cauda equina syndrome) will be excluded. A random subsample of 200 patient participants from each trial period will be referred to a brief self-reported online questionnaire to evaluate the effectiveness of the implementation of the ACI model of care on patient outcomes.

## Randomisation

Before the beginning of the intervention, the four hospitals will be randomly allocated the ‘step’ when the intervention will commence at their emergency department. Randomisation will be conducted using computer-generated random numbers by research staff. Only the research team will be aware of cluster allocation.

## Intervention

A framework has been proposed to facilitate the implementation of research evidence into clinical practice, known as the knowledge-to-action process. This framework links the various types of research enquiry with the key steps in the research translation cycle. The process consists of the knowledge creation cycle and the action cycle and involves end users of research (eg, policy-makers, clinicians and patients) to facilitate engagement with the implementation strategy. We will use this framework to develop a tailored intervention strategy to implement the ACI model of care at the participating emergency departments.

Implementation will begin with visits to each participating emergency department to establish collaborations and approvals. We will also assess organisational issues and potential barriers to the implementation intervention, such as intake and flow of patients with low back pain, assessment of current practices, acceptability of new model and specific roles of emergency clinicians in managing these patients. We will identify existing models of care that are used to guide management of patients presenting with low back pain at each emergency department. Then, we will work with local clinical staff to ensure that each site practices according to the full ACI model of care.

A multifaceted intervention package will be used to implement the ACI model of care at the emergency departments. Briefly, the initial 4-week intervention will consist of printed and electronic educational materials, educational seminars and educational outreach, website support, posters and an audit and feedback approach. Clinician participants will receive a copy of the model and other printed materials, including the ACI consumer information booklet, as well as access to additional online support tools outlined in the ACI model of care, such as web pages and videos, to help them educate their patients. Experienced clinicians, research staff and local opinion leaders (ie, directors of emergency medicine) will deliver the interactive educational seminars and educational outreach. An audit and feedback approach focused on the outcomes of the study will also be used to enhance our implementation programme. A detailed description of the implementation plan for the SHaPED trial can be found in Appendix 3.

The intervention will be tailored for each site by adapting knowledge resources (such as printed decision aids and patient resources) to the local context and by working with local opinion leaders to address potential barriers to implementing the ACI model of care. These instructions, measures and training materials will be hosted online during the implementation phase on The University of Sydney's website. Due to the nature of the intervention, it will not be possible to blind clinician participants to the intervention.

### **Sample size**

Based on the effect size of 10% absolute reduction (from 30% to 20%) in imaging referrals, combined with an alpha of 0.05 and assuming an intraclass correlation coefficient of 0.1, a total number of 1920 low back pain presentations (on average 480 per cluster) to emergency departments is needed for this stepped-wedge cluster trial with 80% power. A preliminary analysis revealed that there were over 2650 low back pain presentations to the participating emergency departments in 2016, showing feasibility of this trial.

### **Outcome measures**

Clinician participants will complete a baseline questionnaire, including demographic questions. They will also be asked to indicate whether they have special interests in low back pain or musculoskeletal medicine, and if they had attended previous continuing medical education or postgraduate training on low back pain management. The outcomes to evaluate the effectiveness of the ACI model of care on health service delivery are routinely collected emergency department measures.

### **Primary outcome**

Proportion of patients receiving any imaging (yes/ no).

## Secondary outcomes

- Proportion of patients receiving advanced imaging (CT/MRI=yes, X-ray/no imaging=no).
- Proportion of patients receiving analgesic medications (topical, oral, injection). Medications will be classified according to the Anatomical Therapeutic Chemical (ATC) classification system (table 3). The ATC classification is recommended by the WHO and is widely used internationally in medication use studies:
  - Paracetamol.
  - Non-steroidal anti-inflammatory drugs.
  - Muscle relaxants.
  - Opioids.
  - Neuropathic pain medications.
  - Other.
- Proportion of patients admitted to:
  - Hospital.
  - Emergency Medical Unit.
  - Short Stay Unit.
- Time in emergency department (triage time to discharge or admission time).
- Proportion of patients referred to specialists (referral for a consultation by the emergency department):
  - Pain management.
  - Rheumatology.
  - Surgery.
- Proportion of patients representing to the emergency department within 48 hours.
- Proportion of patients readmitted to the hospital within 28 days.
- Total health system costs (including intervention costs and health service delivery costs).

**Table 3.** Medications per ATC classification

| Group                      | ATC Code    |
|----------------------------|-------------|
| Analgesics                 | N02B        |
| NSAIDs                     | M01A; M02AA |
| Muscle relaxants           | M03         |
| Opioids                    | N02A; N01AH |
| Neuropathic pain medicines | N03; N06A   |

ATC, Anatomical Therapeutic Chemical; NSAIDs, non-steroidal anti-inflammatory drugs.

Patient outcomes will be collected using a brief online questionnaire that will measure pain intensity (Numeric Rating Scale, range 0–10). We will also use the Patient-Reported Outcomes Measurement Information System (PROMIS) to measure physical function (PROMIS Short Form—Physical Function 4a) and quality of life (PROMIS Scale—Global Health item 1) as advocated by the National Institutes of Health. We have chosen these outcomes as they are considered the three core outcome domains for clinical trials in low back pain identified in a recent Delphi study and by the International Consortium for Health Outcomes Measurement. Patient experience with

emergency service will be assessed using item 31 of the Emergency Department Patient Experience of Care survey advocated by the American College of Emergency Medicine.

### **Data collection methods**

In the week prior to the implementation intervention, the 12-month retrospective baseline health service delivery data will be extracted directly from participating hospitals' electronic record systems. The Sydney Local Health District (SLHD) Targeted Activity and Reporting System (STARS) will be used to access and extract data from SLHD emergency departments. STARS is data analytics programme which monitors clinician performance and service use. At Dubbo Base Hospital, health service delivery data will be extracted from its electronic record system. During the intervention, health service delivery measures will be extracted from all participating emergency departments every week until the end of the 3-month follow-up period. Data extraction will be conducted remotely for all participating emergency departments by research staff blinded to intervention allocation. Data collection through hospitals' electronic systems will also avoid additional workloads within the emergency departments.

Patient outcome measures will be collected using automated text messaging at 1 week (primary time point) and again at 2 and 4 weeks after index emergency department presentation. A random subsample of patient participants will be referred to a brief self-reported online questionnaire containing the Patient Information Statement. Completion of the online questionnaire indicates patient consent to participate in the study. Three reminder messages will be sent to non-responders, and those who do not respond to the third message will be contacted verbally via telephone.

Data will be securely stored in password-protected spreadsheets and transferred to appropriate statistical software for analysis. Spreadsheets will be regularly scrutinised for omissions and errors. Data will be archived at the Sydney School of Public Health, The University of Sydney for 15 years, after which data will be destroyed.

### **Statistical methods**

Data analysis will be performed according to an intention-to-treat analysis, that is, clusters will be analysed according to their randomised cross-over time irrespective of whether cross-over was achieved at the desired time. First, we will investigate temporal trends in healthcare outcomes across the 12-month baseline observation period. In the situation of an underlying temporal trend, we will only include data for the previous 3 months as the baseline observation period. In our primary analysis, the 4-week implementation intervention period will be excluded, but a secondary exploratory analysis will be performed including the implementation period into the intervention group. For the primary outcome analysis, logistic regression models with a random effect for cluster, a fixed effect indicating the group assignment of each cluster at each step and a fixed effect of time (each step) will be used. Data will be analysed using SAS V.9.1.3 (SAS Institute).

### **Economic evaluation**

An economic evaluation of the ACI model of care compared with current emergency practice will be undertaken from the health system perspective. First, we will measure the costs related to the delivery of the intervention (that is, training component, staff time and printed resources). Then, the costs related to health service delivery will be measured via data captured by the hospitals' electronic record systems. Costs will be valued based on government charges, using publicly available data. All costs will be reported in Australian dollars. Where necessary, costs will be converted to 2018 prices using the Australian Institute of Health and Welfare (AIHW) health price index. The incremental cost-effectiveness ratio (ICER) will be presented as the incremental cost per patient avoiding any imaging, opioid prescription and hospital admission.

Univariate sensitivity analyses will be conducted around key parameters likely to influence cost-effectiveness, including cost and efficacy estimates. For example, effectiveness parameters used in the economic evaluation will be

varied over the 95% CIs to assess impact on the ICER. Intervention costs, including training costs, staff time and resource costs will be collected from individual emergency departments and similarly, analysis will examine the effect on the ICER of varying these values over the range reported by participating sites. Bootstrapping will be used to estimate a distribution around costs and health outcomes and to estimate the CIs around the ICER. Results will be plotted on the cost-effectiveness plane.

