## 1.2 Objectives

The overall aim of the SHaPED trial was to evaluate a multi-faceted strategy to implement the ACI model of care for acute low back pain in people who present with low back pain in the ED. The outcomes of the trial reflect the key messages in the model of care:

- (1) patients with non-specific low back pain do not require imaging;
- (2) where medicines are used, simple analgesics should be the first option;
- (3) patients with non-specific low back pain should be managed as outpatients.

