## SHaPED trial Statistical Analysis Plan

- Zopiclone
  - Antiepileptics (N03A):
    - Carbamazepine
    - Ethosuximide
    - Gabapentin
    - Lacosamide
    - Lamotrigine
    - Levetiracetam
    - Oxcarbazepine
    - Phenobarbital
    - Phenytoin
    - Pregabalin
    - Sodium valproate or valproic acid
    - Tiagabine
    - Topiramate
    - Vigabatrin
    - Zonisamide
  - Antidepressants (N06A):
    - Amitriptyline
    - Bupropion
    - Clomipramine
    - Dosulepin
    - Doxepin
    - Duloxetine
    - Duloxetine
    - Fluoxetine
    - Imipramine
    - Mianserin
    - Mirtazapine
    - Moclobemide
    - Nortriptyline
    - Paroxetine
    - Reboxetine
    - Sertraline
    - Venlafaxine
    - Vortioxetine
- Proportion of patients admitted from ED to:
  - Hospital ward
  - Emergency Medical Unit (EMU) or Short Stay Unit (EDSSU)
- Time in ED (triage time to discharge or admission time)
- Proportion of patients referred for a consultation in the ED:
  - Pain management

- Rheumatology
  - Surgery
- Proportion of patients representing to the same ED within 48 hours
- Total health system costs (including intervention costs and health service delivery costs)
- Pain intensity (Numeric Rating Scale, range 0–10)
- Physical function (PROMIS Short Form—Physical Function 4a)
- Quality of life (PROMIS Scale—Global Health item 1)
- Satisfaction (EDPEC survey item 31)

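### The economic evaluation claims a health system perspective but takes its service costs only from hospital records, so care outside those records is omitted, with a bias in the ICER of unknown sign and size

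*Combined protocol and SAP*

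**What the plan says.** The protocol (Economic evaluation) sets the scope: "An economic evaluation of the ACI model of care compared with current emergency practice will be undertaken from the health system perspective". It then names two cost components. The first is delivery of the intervention: training, staff time and printed resources. The second is service use, and "the costs related to health service delivery will be measured via data captured by the hospitals' electronic record systems".

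The cost outcome, in the protocol's Secondary outcomes and again in SAP 1.3.2, is "Total health system costs (including intervention costs and health service delivery costs"). The protocol's Outcome measures section says that the service delivery outcomes "are routinely collected emergency department measures". Its Data collection methods section says that they are "extracted from all participating emergency departments every week until the end of the 3-month follow-up period".

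The ICER is expressed per patient who avoids imaging, opioid prescription and admission, without limiting the imaging to the ED. The primary objective, in both protocol and SAP, does carry that limit.

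One of the model's three key messages is that "patients with non-specific low back pain should be managed as outpatients" (SAP 1.2; also protocol, Objectives). Table 1 of the protocol adds active physical therapy (principle 4), predetermined review (principle 9) and timely specialist referral (principle 10).

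**The concern.** A health system perspective should count care wherever the system provides it. Here the intervention is meant to move some care out of hospital, and care outside the hospital records has no data source. An avoided admission or ED image is credited in full, while any community care that replaces it is not seen.

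The effect unit has the same gap. SAP 2.6.2 treats the absence of an image in the ED dataset as no procedure, so a patient imaged elsewhere after discharge counts as having avoided imaging.

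Cost-effectiveness is a stated secondary objective. The protocol (Ethics and dissemination) intends positive results to support use in other New South Wales departments through a branch of the state health ministry. A funder could read a saving to the hospital as a saving to the system.

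**Working it through.** The plan gives no unit cost, ICER, threshold or expected fall in admissions, so there is no figure to reproduce. The check is a comparison of the text, followed by a scaling calculation on labelled assumptions.

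**1. Scope against sources**

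- Claimed: health system perspective and total health system costs.
- Sourced: intervention delivery, and the hospitals' electronic records.
- Hospital use after the index visit: the protocol lists re-presentation within 48 hours and readmission within 28 days. SAP 1.3.2 keeps re-presentation, to the same ED only, and does not list readmission.
- Patient survey: pain, physical function, quality of life and experience of care. It has no health care use item.
- Not sourced anywhere: general practice, community physiotherapy, community imaging, dispensed medicines, other hospitals.
- Direction of care: outpatient management, review and referral. The protocol's Introduction also says that inpatient care for these patients is probably similar to what primary care could offer, so primary care is the natural substitute.
- SAP: it lists the cost outcome but has no economic section, so the protocol text is the only specification.

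The claimed scope exceeds the sources.

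**2. Effect of omitted cost on the ICER**

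Let E be the absolute reduction in imaging, 0.10 (protocol, Sample size: 30% to 20%). Let d be the net omitted out-of-hospital cost per presentation, intervention minus control. Then

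full ICER − reported ICER = d / E.

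- d = A$10 gives 10 / 0.10 = A$100 per patient avoiding imaging.
- Community care replaces admissions: d = a × c, with a the fall in the admission proportion and c the community cost per shifted patient. Assume a = 0.02 to 0.10 and c = A$100 to A$1000. Then d runs from 0.02 × 100 = A$2 to 0.10 × 1000 = A$100, and the ICER is understated by 2 / 0.10 = A$20 to 100 / 0.10 = A$1000.
- Uncounted savings dominate: assume d = −A$10 to −A$50. The shift is −A$100 to −A$500, and the omission works against the intervention.

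The sign of the bias is the sign of d, which no document gives.

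**3. Imaging moved to after discharge**

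Let f be the share of avoided ED images done later elsewhere, k the cost of each, and C the reported incremental cost per presentation. Then

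corrected ICER = (C + f × E × k) / (E × (1 − f)).

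- If C is positive and k is ignored, the ratio to the reported ICER is 1 / (1 − f). For an assumed f of 0.1 to 0.5 this is 1 / 0.9 = 1.1 to 1 / 0.5 = 2.0. Adding k raises it.
- If C is negative, shrinking the denominator alone makes the ratio more negative, so this factor does not describe a cost-saving result.

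**4. Break-even**

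Write S = −C for a reported saving per presentation. It vanishes when d = S, that is, at S / a per avoided admission. For example, S = A$50 and a = 0.05 (both assumed) give 50 / 0.05 = A$1000. For imaging alone it vanishes when f × k = S / E; S = A$10 (assumed) gives 10 / 0.10 = A$100.

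**The case against.** The strongest objection is to a reading that the steps above may tempt: that the omission must flatter the intervention. The documents do not support it. The Introduction says that needless imaging can cause harm and that opioids carry dependence and overdose. If the model reduces these, later savings in the community are uncounted too. Dispensed medicines could fall. Control-period patients also use community care, including after an admission, and with somewhat more than one-third admitted, nearly two-thirds go home under usual practice anyway. This objection stands in full.

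A reader might also infer that everything after discharge is valued at zero. That holds only for care outside the hospital records. The records cover hospitals and not EDs alone, SAP 2.5 tabulates ward length of stay, and hospital-run clinics may be recorded, although no document says so.

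Third, the shift in care may be modest. The seminars and the audit and feedback (protocol, Appendix 3) concentrate on imaging, opioids and admissions, and nothing quantifies extra reviews or referrals. That bears on size, not on the mismatch.

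Fourth, the ICER unit may be shorthand, since the primary objective already limits imaging to the ED. This is fair, and it makes the correction one of wording.

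Finally, the planned sensitivity analyses cover cost and efficacy parameters in open terms. However, the examples given are effects varied over their confidence intervals and intervention costs varied over the range across sites, and bootstrapping resamples observed costs. None of these reveals a component that was never collected.

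**Conclusion.** The point holds as a mismatch between the stated perspective and the cost sources. As specified, the evaluation is one of hospital and intervention costs, and a conclusion about the whole health system would not follow from it.

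The net bias in the ICER is of unknown sign. It plausibly favours the intervention where community care replaces an admission or an ED image, but this is a judgement about mechanism and not something the documents establish. Its size is not fixed either. The A$20 to A$1000 understatement and the −A$100 to −A$500 reversal both rest on assumed costs and the 10-point design effect. The factor of 1.1 to 2.0 further requires a positive ICER with incremental cost held fixed.

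The issue affects one secondary objective. The primary outcome and the effect estimates are untouched.

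**What to change.** In the protocol's Economic evaluation and SAP 1.3.2:

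- restate the perspective as hospital (ED and inpatient);
- rename the outcome total hospital and intervention costs;
- express the imaging ICER per patient avoiding imaging in the ED, to match the primary objective;
- limit the economic conclusion to that scope.

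Add two parameters to the planned univariate sensitivity analyses, each over a stated range:

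- net out-of-hospital cost per presentation or per avoided admission, with negative values in the range so that direction is not presumed;
- the share of avoided ED imaging done after discharge, with the cost of those images added to the numerator.

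State that the first parameter excludes imaging, so that it is not counted twice. Report for each the value at which any saving vanishes.

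This needs wording and two parameters but no new data. The SAP reports the patient surveys as already completed, so adding a health care use item is probably too late. The downside is a narrower headline economic claim.
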